### Statistical methods for developing a prognostic model

We will develop a prognostic model using logistic regression analysis of candidate variables and a good neurodevelopmental outcome as the primary outcome variable. Multiple imputation (using chained equations) will be used for any variables with missing data considered in the model. Auxiliary variables will be used to aid the imputation. The number of imputed data sets used will be equal to the fraction of missing data.^24^

Box 1 lists all candidate variables. Those variables deemed to be clinically important will be forced into the final model. Candidate variables will be retained if they benefit the model. The process will begin by fitting the full model and then performing backwards elimination, with a conservative significance level of 0.157.^25^ For categorical variables, the category with the lowest p value will dictate whether the variable is included in the final model.

Box 1Patient and cardiac arrest characteristics

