**Patient Demographic**
Age in years.*Presence of PIM-3 ‘high-risk’ comorbidities.†^15^

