**Cardiac arrest characteristics and interventions**
Location of cardiac arrest (IH & OHCA).†OHCA is assigned if chest compressions were initiated before hospital arrival.Aetiology of arrest (cardiac and non-cardiac).†Duration of cardiopulmonary resuscitation.*Continuation of cardiopulmonary resuscitation after Emergency Department arrival (for OHCA only).†.Bystander cardiopulmonary resuscitation.†Initial cardiac rhythm recorded during CA (shockable and non-shockable).†Doses of epinephrine (epinephrine) during cardiopulmonary resuscitation.*Use of continuous vasoactive infusions within 1 hour of PICU admission.†

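### Minor and conditional: the lowest-p-value rule for categorical variables would exceed the stated 0.157 level only if a candidate is coded with three or more levels; one joint test per variable removes the question

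*Protocol article*

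**What the plan says.** All of this is in the protocol article. Under 'Statistical methods for developing a prognostic model', selection starts from the full model and proceeds by "performing backwards elimination, with a conservative significance level of 0.157". For categorical variables, "the category with the lowest p value will dictate whether the variable is included in the final model". No joint test and no adjustment is stated. The same section exempts some predictors from selection: "Those variables deemed to be clinically important will be forced into the final model". Those predictors are not named.

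The section also says "Box 1 lists all candidate variables". Box 1 has 15 items, 5 marked continuous and 10 marked categorical. Five of the categorical items have two levels spelled out, among them "Location of cardiac arrest (IH & OHCA" and "Aetiology of arrest (cardiac and non-cardiac". The other five have no levels spelled out. One of these is "Presence of PIM-3 ‘high-risk’ comorbidities", and another is "Continuation of cardiopulmonary resuscitation after Emergency Department arrival (for OHCA only".

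**The concern.** A variable with k levels enters a logistic model as k − 1 contrasts with a reference category. If the smallest of those k − 1 p values decides retention, the variable gets several chances to pass a threshold meant for one. Its real chance of being kept when it has no effect then exceeds 0.157. Each p value is also a comparison with the reference, so a different reference category can change the decision.

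If this occurred, multi-level noise variables would be favoured over binary and continuous ones, and each would use more than one parameter in a model planned around 75 good outcomes. The question is whether any candidate in this plan is exposed.

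**Working it through.** **1. The stated level.** P(chi-square with 1 df > 2) = 0.1573, so 0.157 is the AIC-equivalent level for a one-parameter term. The corresponding two-sided critical value is |z| > 1.415.

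**2. Levels of the ten categorical candidates (Box 1).**

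| Candidate | Levels |
|---|---|
| Location, aetiology, initial rhythm, day or night, pupils | 2, stated |
| High-risk comorbidity, CPR after ED arrival, vasoactive infusion, inter-hospital transfer | 2, reading the item as yes/no |
| Bystander CPR | not stated; natural reading is yes/no |

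None is listed with three or more.

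**3. Chance of keeping a variable with no effect under the lowest-p rule.** With independent contrasts this is 1 − (1 − 0.157)^(k−1):
- k = 2: 0.157
- k = 3: 1 − 0.843² = 0.289
- k = 4: 1 − 0.843³ = 0.401

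Contrasts that share a reference group are correlated, so the independence figures are only approximate. Large-sample simulation with the correlation included (2,000,000 draws) gives:

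| Levels | Group split | Kept under lowest-p rule |
|---|---|---|
| 2 | equal | 0.157 |
| 3 | equal | 0.267 |
| 3 | 60/30/10 | 0.230 to 0.286, depending on the reference |
| 4 | equal | 0.352 |
| 4 | 40/30/20/10 | 0.296 to 0.381, depending on the reference |

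A 10/45/45 split with the small group as reference gives 0.226. Taking all the three-level results together, the range is about 23% to 29%. Relative to the stated level that is 0.226/0.157 = 1.4 to 0.286/0.157 = 1.8.

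**4. Check at the planned size.** Assumed n = 335: 370 × 0.5 = 185 non-survivors plus 150 survivors followed up, with about 75 events. Results of 20,000 simulated logistic data sets per row, no true effect:

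| Levels | Lowest-p rule | Joint likelihood-ratio test |
|---|---|---|
| 2 | 0.153 | 0.155 |
| 3 (equal; 50/30/20) | 0.269; 0.274 | 0.164; 0.162 |
| 4 (equal) | 0.349 | 0.159 |

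The joint test restores the stated level. At two levels the two rules agree.

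**5. Reference category.** For a three-level variable with no effect, changing only the reference reverses the keep-or-drop decision in about 13% of simulated data sets.

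**6. Can a third level arise?** CPR after ED arrival is defined for out-of-hospital arrests only, but the model pools both settings, so in-hospital children have no yes/no value. One possible coding is in-hospital / out-of-hospital no / out-of-hospital yes. Location is also a candidate, however, and the out-of-hospital indicator equals the sum of the two dummies for that coding. Intercept, location and the two dummies are four columns of rank 3. While location is in the model, only one further contrast (yes versus no among out-of-hospital arrests) can be estimated, and the rule is again a single test. Two contrasts arise only if location is merged into this variable, or is removed while the three levels stay. An extra level for bystander CPR, such as unknown or not applicable, is the other route. Both are assumptions about coding that the article does not show.

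**The case against.** The strongest objection is that the rule does no harm in this plan. Box 1 is presented as the full candidate list, and every categorical item is two-level as stated or as naturally read. The one candidate that suggests three states is collinear with location in the full model. Forced predictors bypass the rule altogether. The bootstrap redevelops the model by the same procedure in each resample, and the coefficients are then shrunk, so some of any extra selection noise would be carried into the optimism correction.

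Most of this stands. A reader might infer that the selected model will be filled with noise variables, or that it already depends on an arbitrary coding choice. The document does not support that, because no listed variable is shown to have more than one contrast. The four-level figures above match no listed candidate and show only how the rule behaves.

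What the objection does not do is justify the sentence. Choosing a category by lowest p value has meaning only when there are at least two contrasts. Either some variable is expected to have three or more levels, and the rule then misses its stated level, or none is, and the sentence does nothing. The bootstrap can reflect extra selection noise in the performance estimates, but it does not change which variables were selected in the original model.

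**Conclusion.** The point holds as a minor, conditional one. For the candidates as worded in Box 1 the rule is one test at 0.157 and there is no inflation. If a candidate is coded with three levels that are all estimable, the rule keeps it by chance about 23% to 29% of the time instead of 15.7%, about 1.4 to 1.8 times the stated level, and the result depends on the reference chosen. These figures assume no true effect and the group splits shown. The finite-sample check also assumes 335 analysed patients and about 75 events. Whether the condition is met cannot be decided from the article, because the coding of five of the ten categorical candidates is not spelled out. The point is no ground for doubting the planned model as it stands.

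**What to change.** Replace the sentence on categorical variables with: *A categorical variable is retained or removed as a whole, using one joint likelihood-ratio or multivariate Wald test of all its levels, pooled over imputations, at 0.157.*

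The cost is one sentence, with no change to data collection or sample size. Two-level variables are essentially unaffected, since the joint test and the single contrast are then asymptotically the same test. The bootstrap already repeats the whole development procedure, so it needs no separate instruction.

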**Patient Demographic**
Age in years.*Presence of PIM-3 ‘high-risk’ comorbidities.†^15^

**Cardiac arrest characteristics and interventions**
Location of cardiac arrest (IH & OHCA).†OHCA is assigned if chest compressions were initiated before hospital arrival.Aetiology of arrest (cardiac and non-cardiac).†Duration of cardiopulmonary resuscitation.*Continuation of cardiopulmonary resuscitation after Emergency Department arrival (for OHCA only).†.Bystander cardiopulmonary resuscitation.†Initial cardiac rhythm recorded during CA (shockable and non-shockable).†Doses of epinephrine (epinephrine) during cardiopulmonary resuscitation.*Use of continuous vasoactive infusions within 1 hour of PICU admission.†
**Service characteristics**
Requirement of inter-hospital transfer prior to PICU admission.†Time of arrest day (07:00–18:59) or night (19:00–06:59).†
**Physiological variables**
Measured for PIM-3 calculation: within 1 hour of PICU admission or within 1 hour of the attendance at the patient’s bedside of a specialist paediatric critical care teamSystolic blood pressure.*Pupillary reaction to light (greater than 3 mm and both fixed and other).†Blood lactate level.**continuous data, †categorical data.IH, in-hospital; OHCA, out-of-hospital cardiac arrest; PIM-3, Paediatric Index of Mortality 3 score.

All continuous variables will be left in their raw form to ensure no data were lost through dichotomisation or categorisation. It will be initially assumed that variables follow a linear trend, before fractional polynomials will be considered using the following powers: -2, –1, −0.5, natural logarithm, 0.5, 1, 2, and 3. A p<0.001 will be required to use a fractional polynomial rather than assuming a linear trend.^26^ The use of fractional polynomials will also be considered for all continuous variables eliminated from the model to check whether this changes their inclusion status.

### Assessment of prognostic model performance

Assessment of the fitted model will be achieved by estimating calibration and discrimination. A calibration plot will be produced by plotting the observed risk against the predicted risk and the calibration slope calculated. We expect the slope should be approximately one as the model developed will be developed using this data. To judge discrimination, the area under the receiver operating curve (equivalent to the C-statistic) and the R squared statistic will be calculated.

### Internal validation of the prognostic model

The model will be internally validated using bootstrap methods. The original data will be used to generate 100 bootstrapped data sets. Each one of these bootstrapped data sets will then be used to develop a prognostic model in the same way as the original model. Estimates of performance (C-statistic and calibration slope) will be obtained from the model fitted using each of the bootstrapped data sets. The estimates obtained from the bootstrapped data sets will be averaged and subtracted from the estimates from the original model to estimate optimism and provide optimism-adjusted performance statistics.

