### Sample size

To reduce problematic bias and improve precision we aim for at least 10 events per variable considered for multivariable modelling.^23^ Following pilot data collection, we calculate 250 CA patients per year are admitted to 27 UK and RoI PICUs, 125 (50%) will survive to PICU discharge and 70 (30%) per year will survive with good neuro-developmental outcome. To test seven variables we estimate a requirement of 70 events (eg, patients with good neurodevelopmental outcome). One hundred per cent of non-survivors will be included (included in PICANet and NET-PACK 3 audit database). We anticipate 80% recruitment and consent rate of remaining survivors. We, therefore, require data collection over an 18-month period to recruit 370 patients. We anticipate that this would ensure successful consent and follow-up of 150 patients, of whom 75 patients are estimated to have a good neurodevelopmental outcome.

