### Final prognostic model

The optimised adjusted calibration slope will then be used as a uniform shrinkage factor. Each of the coefficients from the original model will be adjusted for by multiplying by the shrinkage factor. The intercept will also be adjusted to ensure calibration-in-the-large, the average predicted probability, is the same as the average observed probability.

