### External validation of the NEUROPACK prognostic score

As part of the process of ensuring a prediction model is considered clinically useful, it must be validated in an external dataset.^27^ We aim to do this by validating the NEUROPACK prognostic model in the publically accessible dataset for the Therapeutic Hypothermia After Paediatric Cardiac Arrest OHCA and IHCA randomised controlled trials in the National Institute for Health Biolincc repository (Http://biolincc.nhlbi.nih.gov).^2 3^ The sample size of the dataset to be used for external validation should be sufficient to provide reliable and accurate results. To externally validate the model, predictions of risk for each patient in the external validation dataset are made, and performance statistics, such as the C-statistic, are calculated in the same manner as described earlier.

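### The bootstrap adjustment covers only the C-statistic and calibration slope, so the internal R squared and calibration plot stay apparent values (minor)

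*Protocol article*

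**What the plan says.** Under Assessment of prognostic model performance, the protocol article plans four outputs for the fitted model. Calibration: "A calibration plot will be produced by plotting the observed risk against the predicted risk and the calibration slope calculated". Discrimination and fit: "the area under the receiver operating curve (equivalent to the C-statistic) and the R squared statistic will be calculated". The same section expects a slope of about one, because the model is assessed in the data that produced it.

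Internal validation of the prognostic model then sets up the bootstrap ("The original data will be used to generate 100 bootstrapped data sets") and names what it will estimate: "Estimates of performance (C-statistic and calibration slope) will be obtained from the model fitted using each of the bootstrapped data sets". Optimism is obtained as follows: "The estimates obtained from the bootstrapped data sets will be averaged and subtracted from the estimates from the original model to estimate optimism".

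Under Final prognostic model, the coefficients are shrunk: "The optimised adjusted calibration slope will then be used as a uniform shrinkage factor". The intercept is also adjusted. Under External validation of the NEUROPACK prognostic score, the model is applied to a separate trial dataset, where "performance statistics, such as the C-statistic, are calculated in the same manner as described earlier".

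**The concern.** Four performance outputs are planned and two are named for optimism adjustment. The parenthesis in the bootstrap sentence is a closed list, whereas the external validation sentence uses an open one. Followed literally, the plan yields an adjusted C-statistic and slope next to an unadjusted R squared and an unadjusted plot, all for one model selected in one small dataset.

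R squared tells readers how much of the outcome the model explains, and after variable selection in the same data it is biased upward. The internal plot has two limits. Its slope is one by construction, so it cannot reveal the overly extreme predictions that overfitting produces. It also shows the model before shrinkage, which is not the model put forward for use. The article intends the model for communication with families and for risk stratification, so both outputs should describe how it would perform in new patients.

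**Working it through.** **Sample size, reproduced from the Sample size section.** 250 per year × 1.5 years = 375 patients (stated: 370). 375 × 0.50 = 187.5 survivors, × 0.80 = 150 followed up (stated: 150), × 0.50 = 75 good outcomes (stated: 75). 7 variables × 10 = 70 events (stated: 70). The chain reproduces.

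**Analysis set.** Deaths: 370 × 0.50 = 185. Adding 150 followed survivors gives n = 335, with 75/335 = 22.4% good outcomes. n = 370 was also run, with the same 75 events.

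**Number of candidates.** Box 1 lists 2 demographic + 8 arrest + 2 service + 3 physiological = 15 variables (5 continuous, 10 categorical). 75/15 = 5 events per candidate. The sample size text says "we aim for at least 10 events per variable considered for multivariable modelling" and budgets for seven. Both 7 and 15 are used below.

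**Formula check (no selection).** The article does not say which R squared is meant, so Nagelkerke's is assumed. With event fraction φ = 75/335:

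- Maximum Cox-Snell R² = 1 − exp{2[φ ln φ + (1 − φ) ln(1 − φ)]} ≈ 0.655.
- Likelihood ratio: LR = −n ln(1 − R²_CS).
- Shrinkage: S = 1 − p/LR. Adjusted R² = S × apparent R².

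Example with an assumed apparent value of 0.40: R²_CS = 0.40 × 0.655 = 0.262 and LR = 101.7.

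- p = 7: S = 0.931, adjusted 0.372, excess 0.028.
- p = 15: S = 0.853, adjusted 0.341, excess 0.059.

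Over apparent values of 0.20 to 0.60 and n = 335 or 370, the excess is 0.024 to 0.030 for p = 7 and 0.051 to 0.064 for p = 15.

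**Simulation A (with selection).** Assumptions: 15 independent candidates (5 continuous, 10 binary), 11 with non-zero effects, three signal strengths, about 75 events, backward elimination at 0.157, 200 data sets per setting, and 20,000 new patients as the test set.

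| n | Signal | Apparent R² | R² in new patients | Excess | True slope |
|---|---|---|---|---|---|
| 335 | weak | 0.127 | 0.004 | 0.123 | 0.546 |
| 335 | medium | 0.259 | 0.133 | 0.126 | 0.730 |
| 335 | strong | 0.446 | 0.352 | 0.094 | 0.827 |
| 370 | weak | 0.129 | 0.010 | 0.119 | 0.565 |
| 370 | medium | 0.251 | 0.123 | 0.127 | 0.720 |
| 370 | strong | 0.443 | 0.323 | 0.119 | 0.794 |

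The apparent slope was 1.000 in every setting. If predictions are recalibrated in the test set, which is a best case for shrinkage, the gap is still about 0.08 to 0.10 (for example 0.446 − 0.369 = 0.077 and 0.251 − 0.150 = 0.101).

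**Simulation B (does the correction work?).** Assumptions: n = 335, 15 candidates, 7 with real effects, latent correlation 0.2, 60 data sets per scenario, 100 bootstrap samples each. Weaker model: apparent 0.229, new patients 0.128, bootstrap-corrected 0.105. Stronger model: 0.366, 0.266 and 0.253. The excess is about 0.10 in both. The corrected values lie within 0.023 and 0.013 of the new-patient values, slightly on the low side.

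**Not modelled.** The fractional polynomial search and the rule that the category with the lowest p value decides inclusion could both add optimism. The article also lets candidates be dropped for practicality, which could reduce it.

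**The case against.** Four objections have force.

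1. A reader might infer that R squared and the calibration plot are never assessed outside the development data. The article does not support that. The external validation sentence has an open list and refers back to the measures already described, which can include both. This narrows the point to the internal figures. Results in a different trial population do not correct those.

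2. A reader might infer that the internal plot will look near perfect whatever the model's quality. That goes too far. Maximum likelihood fixes the slope at one but does not put the curve on the diagonal. Local misfit can show, for example where linearity is kept because a fractional polynomial missed p<0.001. The plot is a legitimate check of fit. What it cannot show is miscalibration from overfitting.

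3. A reader might infer that the published R squared will be substantially inflated. The article states neither an expected R squared nor which value will be published, and the excess runs from minor to material depending on the assumptions.

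4. The article is a condensed account, acknowledges that the apparent slope should be near one, and uses the slope rather than R squared for shrinkage. No coefficient depends on R squared. This limits the severity. It does not remove the point, because the article does state which measures the bootstrap covers, and R squared, named in the section just before, is not among them.

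It can also be said that the optimism step itself is the larger problem at this place: the text does not describe applying the bootstrap models to the original data. That is a separate matter, but adding R squared to the step as written would not yield a valid correction, so the fix has to cover both.

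**Conclusion.** The point holds in a limited form and is minor. The internal validation text provides no optimism adjustment for the R squared and calibration plot that the preceding section plans, so both remain apparent values, and the plot is not of the final shrunken model.

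The size rests on assumptions, since the article gives no expected R squared. The low end, about 0.03, applies if seven parameters are fitted without selection. The high end, 0.09 to 0.13, is closer to the procedure described, which fits all of Box 1 and then eliminates backwards. The formula without selection for 15 parameters lies between, at 0.05 to 0.06. The true slopes of 0.55 to 0.83 in simulation A, against an apparent 1.000, show what the internal plot would miss under those assumptions. The consequence is for how performance is reported, not for the model's coefficients.

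**What to change.** - In Internal validation of the prognostic model, change the list in the parenthesis to: C-statistic, R squared and calibration slope.
- State that each bootstrap model, rebuilt with the full selection procedure, is evaluated both in its own bootstrap sample and in the original data. Optimism is the average difference between the two, subtracted from the apparent value.
- Name the type of R squared, and report the optimism-adjusted value alongside the adjusted C-statistic.
- In Assessment of prognostic model performance, label the R squared and calibration plot as apparent.
- Add a bootstrap-corrected calibration curve for the model defined under Final prognostic model.

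Cost: a few lines of analysis text and code, no new data, and the same bootstrap samples. The reported R squared becomes less favourable. The R squared and plot changes leave the coefficients and predicted risks untouched. Evaluating bootstrap models in the original data also bears on the adjusted slope, and so on the shrinkage factor, but that follows from repairing the optimism step and not from adding R squared or the curve.

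### The bootstrap optimism formula leaves out testing the bootstrap models in the original data; read literally it yields practically no shrinkage and a wrong-signed C-statistic correction

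*Protocol article*

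**What the plan says.** The relevant text is in three consecutive sections of the protocol article.

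- *Assessment of prognostic model performance*, on the calibration slope in the development data: "We expect the slope should be approximately one as the model developed will be developed using this data".
- *Internal validation of the prognostic model*: "The original data will be used to generate 100 bootstrapped data sets". The whole model-building process is repeated in each: "Each one of these bootstrapped data sets will then be used to develop a prognostic model in the same way as the original model". Then: "Estimates of performance (C-statistic and calibration slope) will be obtained from the model fitted using each of the bootstrapped data sets". Optimism is defined by one subtraction: "The estimates obtained from the bootstrapped data sets will be averaged and subtracted from the estimates from the original model to estimate optimism".
- *Final prognostic model*: "The optimised adjusted calibration slope will then be used as a uniform shrinkage factor", and "Each of the coefficients from the original model will be adjusted for by multiplying by the shrinkage factor".

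So one performance value is described per bootstrap model. The data in which it is measured are not named, and testing in the original data is not mentioned.

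**The concern.** Bootstrap optimism needs two values for each bootstrap model: its performance in the bootstrap sample it was built on, and its performance in the original data. The gap between them measures overfitting. The plan describes one value and compares it with the apparent performance of a different model, the original one.

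If that one value is performance in the bootstrap sample itself, two apparent performances are being compared, and the plan's own remark about a slope near one applies to both. The slope correction then vanishes, and with it the shrinkage that the next section relies on.

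At stake are the final coefficients and the reported internal validation. An overfitted model without shrinkage gives predictions that are too extreme, in a tool meant for talking with families and for risk stratification. The *Secondary analysis* section repeats the same steps for the supplementary models.

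**Working it through.** **The plan's own figures.** *Sample size* section: 7 × 10 = 70 events; 250 × 1.5 = 375 patients (370 stated); 370 × 0.5 × 0.8 = 148 followed up (150 stated); 150 × 0.5 = 75 good outcomes. These reproduce to within rounding. Box 1 lists 15 candidates, so 75 / 15 = 5 events per candidate, against the 10 aimed for. Overfitting is therefore a live issue.

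**Algebra.** Let O be the original model's apparent performance, B the mean performance of the bootstrap models in their own samples, and T their mean performance in the original data.

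- Literal reading: optimism = O − B, so adjusted = O − (O − B) = B.
- Charitable reading (bootstrap models tested in the original data): optimism = O − T, so adjusted = T.
- Standard method: optimism = B − T, so adjusted = O − (B − T).

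*Slope.* The model is an unpenalised logistic regression. Its calibration slope in its own complete data is 1, so O = B = 1. The literal reading gives optimism 1 − 1 = 0 and shrinkage factor 1. The charitable reading gives T. The standard method gives 1 − (1 − T) = T, the same.

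*C-statistic.* Bootstrap models fit their own samples better than the original model fits its own, so B > O in every scenario below. Literal optimism is then negative, and subtracting it raises C. The charitable optimism O − T is smaller than B − T by B − O.

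**Simulation for size.** Assumed, because the document does not give them:

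- N = 335 (370 × 0.5 = 185 deaths, plus 150 survivors followed) and about 75 events.
- Predictor effects, with a mix of continuous and binary predictors and complete data.

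Taken from the plan: backward elimination at 0.157 and 100 bootstraps. There were 40 replicates, and true values come from 100,000 new patients.

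| | 15 candidates, weaker effects | 15 candidates, stronger effects | 7 candidates |
|---|---|---|---|
| Shrinkage, literal | 1.00 | 1.00 | 1.00 |
| Shrinkage, charitable and standard | 0.75 | 0.80 | 0.86 |
| True slope | 0.77 | 0.80 | 0.85 |
| C apparent (O) | 0.7687 | 0.8566 | 0.7510 |
| C adjusted, literal (B) | 0.7985 | 0.8767 | 0.7648 |
| C adjusted, charitable (T) | 0.7470 | 0.8406 | 0.7353 |
| C adjusted, standard | 0.7173 | 0.8205 | 0.7216 |
| C true | 0.7194 | 0.8146 | 0.7212 |

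Literal slope optimism never differed from zero by more than 4e-16. Literal C optimism was −0.030, −0.020 and −0.014.

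Charitable against standard C optimism:

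- 15 candidates, weaker effects: 0.7687 − 0.7470 = 0.0217 against 0.7985 − 0.7470 = 0.0515 (42%).
- 15 candidates, stronger effects: 0.0160 against 0.0361 (44%).
- 7 candidates: 0.0157 against 0.0295 (53%).

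A further simulation (15 candidates, other assumed effects, 120 replicates) gave standard shrinkage of 0.73 and 0.80, against true slopes of 0.67 and 0.77. The literal factor was again 1.000. Charitable C optimism was 0.024 against 0.058 (41%) and 0.017 against 0.035 (49%).

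**Multiple imputation.** The plan imputes missing predictors, and pooled coefficients need not give a slope of exactly 1. A run with seven predictors, no selection, 12 replicates and 50 bootstraps gave literal shrinkage factors of 0.998 (10% missing) and 0.993 (30% missing). Testing the bootstrap models in the original data gave 0.88 and 0.87.

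**The case against.** A reader might infer that the final model is bound to be published unshrunk. The document does not support that. The internal-validation section names the model whose performance is taken, not the data in which it is measured. Three features point to testing in the original data:

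- Original minus bootstrap average gives positive optimism only on that reading.
- The authors know that the slope is about one in a model's own data.
- A shrinkage step would be pointless if the factor were always one.

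On that reading the slope and shrinkage factor match the standard method. These points stand, so the loss of shrinkage is a consequence of one reading, although the more literal one: the sentence averages estimates said to come from the bootstrapped data sets.

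A reader might also call the slope optimism exactly zero. That holds for complete data only. With the planned imputation it is near zero, which makes little practical difference.

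The simulated sizes depend on assumed effects, and the 15-candidate figures show the worse case. The study was sized for seven variables, and the section on predictive factors leaves final candidate selection open.

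Lastly, external validation in the hypothermia trial datasets could expose overfitting. That would detect unshrunk coefficients but not repair them.

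The charitable reading does not rescue the C-statistic. The stated subtraction under-corrects it even then, so this is more than a detail left for an analysis plan.

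**Conclusion.** The formula is wrong as written. On neither reading does it give a correct optimism-adjusted C-statistic. On the literal reading it also makes the planned shrinkage practically inert (factor about 0.99 to 1.00) and moves C in the wrong direction, by 0.014 to 0.030 in the tabulated scenarios. On the charitable reading the final coefficients are right and the harm is confined to reporting, with C optimism understated by roughly half.

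The slope result on the literal reading follows from the fitting method and does not depend on the assumed effects. The sizes do: correct shrinkage of about 0.73 to 0.80 with 15 candidates and about 0.86 with seven rests on N of about 335, about 75 events and invented predictor effects, and is illustrative.

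**What to change.** Replace the last sentence of *Internal validation of the prognostic model* with:

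> The C-statistic and calibration slope of each bootstrap model will be calculated (a) in its own bootstrap sample and (b) in the original data; optimism is the mean of (a − b) over the bootstrap samples and is subtracted from the apparent performance of the original model; the optimism-adjusted slope is the shrinkage factor.

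The instruction to repeat the full model development in every bootstrap sample is already there and can stay.

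The cost is one extra evaluation per bootstrap sample and a less favourable reported C-statistic. No additional patients or data are needed.
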